### Outcome measures

2.11

#### Primary outcome

2.11.1

1-year DFS rate: Refers to the proportion of patients who did not experience recurrence, metastasis, or death (from any cause) within 1 year following surgery. Although OS is the gold standard for evaluating malignant tumor treatment, given the strong correlation between DFS and OS and to control of time costs, the 1-year DFS rate was selected as the primary endpoint to explore long-term efficacy (22).

#### Secondary outcomes

2.11.2

(1) Prognosis-related indicators:

DFS: Time from randomization to tumor progression or death (from any cause).Overall survival (OS): Time from randomization to death (from any cause).Cumulative annual recurrence and metastasis rate for 1–3 years: Proportion of patients experiencing recurrence and metastasis from the day of surgery to 1, 2, and 3 years.Cumulative annual survival rate for 1–3 years: Proportion of patients surviving from the day of surgery to 1, 2, and 3 years.

(2) Indexes associated with fat distribution:

Total, Visceral, and Subcutaneous Fat Areas: These measure fat areas on cross-sectional images obtained through plain CT scanning.Visceral Adiposity Index: A new assessment of visceral fat based on waist circumference (WC), body mass index (BMI), triglyceride (TG), high-density lipoprotein (HDL), and visceral adiposity index (VAI). Male VAI = during [WC/(39.68 + 1.88 × BMI)] × (TG/1.03) × (1.31/HDL). Female VAI = during [WC/(36.58 + 1.89 × BMI)] × (TG/0.81) × (1.52/HDL).

(3) Tumor markers: squamous cell carcinoma antigen (SCC), carcinoembryonic antigen (CEA), carbohydrate antigen 19-9 CA199), and cytokeratin-19-fragment (CYFR21-1).(4) Peripheral blood inflammatory index: lymphocyte-to-monocyte ratio (LMR); lymphocyte-to-neutrophil ratio (LNR).(5) Prognostic nutritional index: Serum albumin level (g/L) + 5 × total number of peripheral blood lymphocytes (×10^9/L).(6) Symptoms and quality of life evaluation:

Quality of life of the patient: This score was assessed using the Quality of Life Questionnaire Esophageal-Specific Module 18(QLQ-QES18). Each of the 18 questions is scored from 1 to 4, with a total score ranging from 18 to 72. A higher score indicates poorer quality of life.Evaluation of the symptoms of the patients: This score was measured using the M. D. Anderson Symptom Traditional Chinese Medicine (MDASI-TCM). Each of the 26 questions was rated on a scale from 0 to 10, resulting in a total score ranging from 0 to 260. A higher score indicated more severe symptoms.

(7) Medication compliance: The number of cases and percentages were calculated for <80, 80–120, and >120% compliance.(8) Percentage of Participants with Adverse Events: Percentage of participants experiencing adverse events in different study arms.

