## Abstract

**Background:**

Esophageal cancer (EC) is a malignant tumor with a high recurrence and metastasis rate and poor prognosis. In 2024, China ranked first in the world in terms of new EC cases and deaths. Surgery is the main treatment method for EC, but the clinical difficulty is how to prevent recurrence and metastasis after surgery. Traditional Chinese medicine as a complementary therapy has played an important role in this regard. Preclinical studies have confirmed that Qizhu Yuling Prescription (QZYLP) has anticancer effects, reduces treatment side effects, and improves quality of life, except for the lack of long-term prognostic results. Therefore, this study aims to investigate whether QZYLP can reduce the recurrence and metastasis rates of EC after surgery, improve disease-free survival (DFS), prolong overall survival, and observe the safety of the drug.

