### Drop out criteria

2.5

Patients who are unable to adhere to the treatment owing to unforeseen events during the study.Participants who voluntarily request to withdraw from the study.Participants with poor adherence to the study protocol as determined by the investigator.Pregnancy, death, or loss of contact with the participant.

Following termination of treatment or withdrawal from the study, they entered a follow-up period. They received periodic follow-ups (every 3 months, with telephone follow-up accepted) to assess survival status, extending for at least 3 years post-operation.

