### Sample size calculation

2.9

This study is a RCT. The test group was administered QZYLP Granules, while the control group was placed on a placebo. The primary outcome measure was the postoperative DFS of patients. The study was designed as a superiority trial with a 1:1 ratio between the test and control groups. According to the literature, the mDFS for patients with lymph node-positive esophageal squamous carcinoma after surgery with adjuvant therapy is 19.3 months (19). Assuming that the DFS of the test group was 12 months longer than that of the control group, with α=0.05 and 1-β=0.80, the expected time to enroll all participants was 24 months, and the total duration of the clinical trial was expected to be 36 months, with a consistent enrollment rate of the study participants. Using PASS 11 software, it was calculated that 140 cases were needed in each of the test and control groups. Considering a 10% dropout rate, 155 participants were enrolled in the test and control groups, resulting in a final number of 310 participants. The following formula was used (20). Here δ=π_1_-π_2_.

$$n={\left(\frac{u_{\alpha }+u_{\beta }}{\delta }\right)}^{2}[\pi_{1}(1-\pi_{1})+\pi_{2}(1-\pi_{2})]$$

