### Statistical analysis

2.14

Statistical software: SAS 9.4 statistical software will be utilized to analyze effective indicators using the Full Analysis Set and Per Protocol Set analyses. A safety data set analysis will be performed for adverse reactions.

Statistical methods: All statistical tests will be two-sided, with *P*≤ 0.05 considered statistically significant for the differences tested. Data will be analyzed for outliers, which are professionally evaluated to determine appropriate trade-offs. Missing values will also be professionally analyzed to determine whether to classify them as dropouts or data transfers. The proportion of missing cases should not exceed 10%; otherwise, they should be analyzed and explained. Measurement data will be described using mean, standard deviation, median, minimum, and maximum values. Count data will be described using frequency and percentage. The *T*-test and rank-sum test, among others, will be employed to analyze measurement data, while the chi-square test and Ridit analysis will be used for count data. Survival data will be analyzed using the Kaplan–Meier method, Wilcoxon rank-sum test, and log-rank test. For multifactorial survival analysis, the Cox proportional risk regression model will be used. To reveal whether there are differences in effects between different feature groups, subgroup analyses will be performed on subgroups for sex, age, occupation, health status (smoking, alcohol using, hypertension, diabetes, etc), type of operation, and adjuvant therapies.

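### The 1- to 3-year recurrence and metastasis rates leave out death, and no method named in the plan estimates them correctly when there are both deaths without recurrence and incomplete follow-up

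*Protocol article*

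**What the plan says.** Section 2.11.2 lists, among the prognosis-related secondary outcomes, the cumulative annual recurrence and metastasis rate: "Proportion of patients experiencing recurrence and metastasis from the day of surgery to 1, 2, and 3 years". The same list defines DFS as "Time from randomization to tumor progression or death (from any cause"), so death counts as an event there. It also counts in the primary endpoint (section 2.11.1), but not in the recurrence rate.

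Section 2.14 describes the analysis by type of data. For times to event: "Survival data will be analyzed using the Kaplan–Meier method, Wilcoxon rank-sum test, and log-rank test", and "For multifactorial survival analysis, the Cox proportional risk regression model will be used". For counts: "the chi-square test and Ridit analysis will be used for count data". It does not say which group the recurrence rate belongs to, and it names no competing-risk method.

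Section 2.5 includes in one drop-out criterion "Pregnancy, death, or loss of contact with the participant". After withdrawal, patients are contacted every 3 months, by telephone if need be, for survival status; recurrence is not mentioned.

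The Abstract puts first among the aims "whether QZYLP can reduce the recurrence and metastasis rates of EC after surgery".

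**The concern.** A patient who dies without recurrence can no longer recur. A rate that counts recurrence only therefore needs an estimator that treats such deaths as final and patients with short follow-up as censored. The two routes that section 2.14 leaves open each manage one of these.

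- **Kaplan-Meier of time to recurrence.** This handles short follow-up. If deaths are censored, however, the dead are treated as if they could still recur, and 1 minus Kaplan-Meier exceeds the proportion who actually recur.
- **Crude proportion with chi-square.** A patient who died without recurrence is correctly counted as not having recurred. A patient lost early, or not yet followed to the time point, is also counted as recurrence-free, so the rate is too low.

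Section 2.5 adds to the uncertainty by placing death alongside loss of contact, which invites the same handling for both. What is at stake is the accuracy of the only outcome that isolates recurrence from death, in a trial whose first stated aim is to reduce recurrence.

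**Working it through.** **Inputs from the article.** Section 2.9: "the mDFS for patients with lymph node-positive esophageal squamous carcinoma after surgery with adjuvant therapy is 19.3 months"; the test arm is assumed 12 months longer (31.3 months); α = 0.05, power 0.80, 24 months of uniform accrual within 36 months in total, 140 per arm, 155 after 10% dropout. Section 2.14: two-sided tests. Section 2.1: follow-up to 3 years after surgery.

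**Assumptions not in the article.** Exponential DFS, and a share f of first DFS events that are deaths without recurrence, varied from 5% to 30%.

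**Step 1: reproduce the plan's own figure.** The DFS hazards are ln 2/19.3 = 0.0359 and ln 2/31.3 = 0.0221 per month, so HR = 19.3/31.3 = 0.617. Schoenfeld's formula gives 4 × (1.96 + 0.84)²/(ln 0.617)², or 135 events. Event probabilities under the stated accrual are 0.564 and 0.405, and 135/(0.564 + 0.405) gives about 139, so 140 per arm. Then 140/0.9 = 155.6, that is 156 against 155 stated. The exponential model is thus consistent with the plan. The sample size rests on DFS and is not touched by this point.

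**Step 2: 1 minus Kaplan-Meier against cumulative incidence.** With DFS function S(t) and the same share f throughout:

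- 1 − KM = 1 − S(t)^(1−f)
- cumulative incidence (CIF) = (1 − f) × (1 − S(t))

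At 36 months S is 0.274 (control) and 0.451 (test). Example for control, f = 10%: 1 − 0.274^0.9 = 68.8%; 0.9 × (1 − 0.274) = 65.3%.

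Results at 36 months, in %, if treatment has the same HR of 0.617 on both causes (excesses computed before rounding):

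| f | Control 1−KM / CIF | Excess | Test 1−KM / CIF | Excess | Gap 1−KM / CIF |
|---|---|---|---|---|---|
| 5% | 70.7 / 68.9 | 1.8 | 53.1 / 52.2 | 0.9 | 17.6 / 16.7 |
| 10% | 68.8 / 65.3 | 3.5 | 51.2 / 49.4 | 1.8 | 17.6 / 15.8 |
| 20% | 64.5 / 58.0 | 6.4 | 47.2 / 44.0 | 3.2 | 17.3 / 14.1 |
| 30% | 59.5 / 50.8 | 8.8 | 42.8 / 38.5 | 4.3 | 16.8 / 12.3 |

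At 12 months the control excess is 0.3 (f = 5%) to 1.5 points (f = 30%), and the test-arm excess 0.1 to 0.6.

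**Step 3: direction of the error in the gap.** In the table 1 − KM overstates the gap, by 0.9 to 4.5 points at 36 months. If the death hazard is instead equal in both arms and the total DFS hazards are kept, the overstatement is 0.4 to 3.4 points. Now keep the recurrence hazards at 85% of each planned DFS hazard, and set the hazard of death without recurrence at 0.15 (control) and 0.30 (test) of the control DFS hazard. The 36-month gap is then 17.5 points by 1 − KM and 20.0 by CIF, so 1 − KM understates it. (In this scenario the test arm's total DFS hazard is above the planned one.)

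**Step 4: the crude proportion, f = 15%.** With complete follow-up it equals the CIF. Two cases of incomplete follow-up:

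- 10% lost evenly over 36 months: crude 59.2% v CIF 61.7% (control), 44.6% v 46.7% (test).
- The 36-month total read as a data cut, with entry 6 months after surgery (both assumptions): follow-up from randomization runs from 12 to 36 months and 3 years from surgery needs 30, so (30 − 12)/24 = 75% of patients fall short. The crude 3-year rates are 47.3% v 33.8% against CIF 56.1% v 41.3%; the gap is 13.5 instead of 14.8 points.

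Steps 2 and 3 put 12 and 36 months on the clock of the planning model. On the surgery clock of the second case in Step 4, the 3-year control figure is 60.0% by 1 − KM against 56.1%, an excess of 3.9 points where the 36-month calculation at f = 15% gives 5.0.

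**The case against.** The strongest reply is that the article never assigns Kaplan-Meier to this rate. It calls the outcome a proportion, and the plainest reading is a count over all patients. With follow-up to 3 years, as section 2.1 plans, that proportion is a valid cumulative incidence and does not miscount the dead. The choice of estimator for one secondary outcome could also wait for the statistical analysis plan. A log-rank test or Cox model with deaths censored is, moreover, a legitimate comparison of the hazard of recurrence, and both are already named.

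Most of this stands. What it leaves is the estimate of the proportion itself when follow-up is incomplete. The plan expects 10% dropout, follows withdrawn patients for survival status only, and gives no rule for unknown recurrence status beyond case-by-case judgement of missing values.

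Four stronger readings are tempting, and the documents do not support them:

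- *The plan will report 1 minus Kaplan-Meier.* Nothing says so.
- *The benefit will look too large.* Step 3 shows that the sign depends on how treatment affects death without recurrence, which is unknown.
- *The dead will be removed from the denominator.* Section 2.5 lists death among drop-out criteria, but nowhere excludes those patients from analysis, and section 2.14 names a Full Analysis Set.
- *Censoring deaths lets an excess of early deaths pass for prevention.* That weakness belongs to the crude proportion and to cumulative incidence. It is why deaths must be shown beside the recurrence rate. Survival rates, OS and DFS, all planned, give part of that picture.

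**Conclusion.** The point holds in a limited form. The outcome excludes death, the estimator is left open, and none of the named methods gives the right proportion when deaths without recurrence and incomplete follow-up occur together. The error is upward with 1 minus Kaplan-Meier and downward with a crude proportion. Its size cannot be fixed from the article, because the share of deaths without recurrence is not given; the 3-year range of 1.8 to 8.8 points in controls rests on the assumed 5% to 30% and on exponential DFS with the planning medians. At 1 year it is at most about 1.5 points. The outcome is secondary, and the primary endpoint and DFS include death and are not affected. It is worth correcting because the remedy is cheap and the rate answers the first aim in the Abstract.

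**What to change.** State in sections 2.11.2 and 2.14, or in the analysis plan, that:

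- the 1-, 2- and 3-year recurrence and metastasis rates are estimated by cumulative incidence (Aalen-Johansen), with death without recurrence as a competing event;
- patients lost to recurrence follow-up are censored at their last recurrence assessment;
- arms are compared with Gray's test (cumulative incidence) or a cause-specific Cox model (hazard of recurrence), with the choice fixed in advance;
- the cumulative incidence of death without recurrence is shown beside it for each arm;
- for this outcome death is a competing event and not a drop-out, notwithstanding the list in section 2.5.

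The cost is a few sentences and slightly more analysis work. One limit remains: withdrawn patients followed only for survival status may have unknown recurrence status, including some later known to have died. The plan should say how they are handled and report their number by arm.

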#### Safety outcomes

2.11.3

Routine blood/urine/stool tests, liver and kidney function, and electrocardiogram (ECG), among others.

### Adverse events observation and recording

2.12

Adverse event monitoring in this study followed the Common Terminology Criteria for Adverse Events developed by the U.S. Department of Health and Human Services. All adverse events experienced by participants during the study were documented in the Case Report Form (CRF). Adverse events were identified through self-reports by participants, test results, and retrospective review of medication co-administration. Upon the occurrence of an adverse event, the investigator assessed whether the participant should continue in the study based on the severity. Cases where participants discontinued the trial owing to serious adverse events were followed up, and their outcomes were documented.

### Data collection and management

2.13

#### Data collection

2.13.1

Raw data will be obtained from the medical records of the participants, test and examination reports issued by medical institutions at all levels, and patient interview scale data. Investigators at each sub-center will collect and enter this information into paper CRFs. The study data will be managed using the Jdhhealth Multi-center research collaboration platform, an Electronic Data Capture System (EDC) hosted by Beijing Jiudu Jiade Technology Co. Jdhhealth is a secure web-based platform for data collection, tracking, verification, and export. It supports multi-user access and prevents unauthorized entry through established security protocols.

#### Data management

2.13.2

Two trained researchers will perform double data entry consecutively. The EDC system will be used to compare and verify the double data entry, after which the researchers conduct final data modification and validation. The EDC system will keep a log of data changes. Participants will be identified in the system by code rather than by name. Once data quality control is finalized, the database will be locked. The researchers will assume data monitoring responsibilities.

### Statistical analysis

2.14

Statistical software: SAS 9.4 statistical software will be utilized to analyze effective indicators using the Full Analysis Set and Per Protocol Set analyses. A safety data set analysis will be performed for adverse reactions.

Statistical methods: All statistical tests will be two-sided, with *P*≤ 0.05 considered statistically significant for the differences tested. Data will be analyzed for outliers, which are professionally evaluated to determine appropriate trade-offs. Missing values will also be professionally analyzed to determine whether to classify them as dropouts or data transfers. The proportion of missing cases should not exceed 10%; otherwise, they should be analyzed and explained. Measurement data will be described using mean, standard deviation, median, minimum, and maximum values. Count data will be described using frequency and percentage. The *T*-test and rank-sum test, among others, will be employed to analyze measurement data, while the chi-square test and Ridit analysis will be used for count data. Survival data will be analyzed using the Kaplan–Meier method, Wilcoxon rank-sum test, and log-rank test. For multifactorial survival analysis, the Cox proportional risk regression model will be used. To reveal whether there are differences in effects between different feature groups, subgroup analyses will be performed on subgroups for sex, age, occupation, health status (smoking, alcohol using, hypertension, diabetes, etc), type of operation, and adjuvant therapies.

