### Interventions

2.10

The experimental group was administered QZYLP granules. Patients were administered two small packets in the morning and two small packets in the evening. The medication was dissolved in hot water before administration. Each course of treatment lasted 4 weeks, with six courses in total. The patients will be followed up for up to 3 years after their EC surgery.

The control group was administered a placebo. The placebo was designed to be identical to the experimental drug in terms of the outer packaging, color, shape, and taste. It was prepared from maltodextrin and food coloring. The raw materials of maltodextrin conformed to the relevant provisions of excipients - maltodextrin in the *Chinese Pharmacopoeia 2015 edition, Part Four* (21). The food coloring included caramel coloring, egg yolk coloring, and milk chocolate brown pigment, all of which were edible-grade ingredients. The dosing method was comparable to that of the experimental group.

During the experimental treatment, drugs for managing myelosuppression, nausea and vomiting, diarrhea, abnormal liver and kidney functions, infections, and other symptomatic treatments were allowed concurrently. However, the specific symptoms and the combined use of these drugs were accurately recorded. The following were prohibited: (1) Other antitumor therapies (including chemotherapy, immunotherapy, molecular targeted therapy, and radiotherapy) (2) Chinese herbal decoctions, Chinese herbal injections, and Chinese patent medicine with antitumor effects.

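### For continuous secondary outcomes measured at lead-in and repeatedly over six courses, the article names only two-sample tests; a baseline-adjusted repeated-measures model with one prespecified contrast would be more precise

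*Protocol article*

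**What the plan says.** Section 2.14 (Statistical analysis) gives the method for continuous data in one sentence: "The *T*-test and rank-sum test, among others, will be employed to analyze measurement data". It adds "All statistical tests will be two-sided" and sets significance at P ≤ 0.05. The one regression model in the section is Cox, for survival data. No visit or contrast is singled out for the continuous outcomes.

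Section 2.10 (Interventions) sets the length of treatment: "Each course of treatment lasted 4 weeks, with six courses in total". Table 1 ticks MDASI-TCM, QLQ-QES18, tumour markers and fat-distribution indices in the lead-in period and at the end of courses 1, 2, 3 and N. Tumour markers and fat indices are also ticked in follow-up, every 3 months; the two questionnaires are not.

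Section 2.11.2 (Secondary outcomes) treats the questionnaires as total scores. For MDASI-TCM: "Each of the 26 questions was rated on a scale from 0 to 10, resulting in a total score ranging from 0 to 260". QLQ-QES18 is a total from 18 to 72.

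**The concern.** The data are longitudinal and have a baseline, while the methods named compare two groups on one value per patient. Such a test has no place for the baseline value as a covariate and takes nothing from a patient's other visits. Three things follow.

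- **Precision.** Symptom scores and blood markers usually correlate with their own baseline. A comparison that does not adjust for it carries avoidable variance.
- **Choice of visit.** With up to six post-baseline values per outcome and no lead time point, nothing in the article prevents several tests per outcome or selection of a favourable visit afterwards.
- **Who contributes.** Section 2.1 moves patients into follow-up after an endpoint event, and Table 1 has no MDASI-TCM or QLQ-QES18 in follow-up. Section 2.5 follows patients who stop treatment for survival status, with telephone contact accepted. A simple test at the end of course 6 would therefore rest on patients still under assessment.

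The Discussion says the lipid and immune outcomes were chosen to show how the drug works, so these comparisons are meant to carry part of the interpretation.

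**Working it through.** **The plan's own figure.** The article gives no sample size, SD or target difference for the continuous outcomes. Its only sample-size figure is for DFS (section 2.9): control median "after surgery with adjuvant therapy is 19.3 months", 12 months longer on test, "with α=0.05 and 1-β=0.80". With exponential DFS, HR = 19.3/31.3 = 0.617. Schoenfeld's formula, 4(1.96 + 0.84)²/(ln 0.617)², gives 135 events. With 24 months' uniform accrual and 36 months in total, the event probabilities are 0.564 and 0.405, mean 0.485. Then 135/(2 × 0.485) = 139.2, which agrees with the stated 140 per arm. That figure does not depend on the present point.

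**Inputs for the check.**
- Six post-baseline visits: section 2.10 and Table 1.
- Two-sided 0.05: section 2.14.
- 140 per arm with values: section 2.9, before dropout.
- Correlation r between baseline and follow-up, and between visits: assumed, since the article gives none.
- Equal variance at baseline and follow-up, and a true difference of 0.3 SD: assumed, for illustration.

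**Step 1: variance relative to a t-test of the follow-up value (= 1).** A t-test of change from baseline has 2(1 − r); baseline adjustment has 1 − r². The saving from adjustment is r² against follow-up values and, against change, 1 − (1 − r²)/[2(1 − r)] = (1 − r)/2.

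| r | change score | adjusted | saving vs follow-up only | saving vs change |
|---|---|---|---|---|
| 0.5 | 1.00 | 0.75 | 25% | 25% |
| 0.6 | 0.80 | 0.64 | 36% | 20% |
| 0.7 | 0.60 | 0.51 | 49% | 15% |

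**Step 2: power for a 0.3 SD difference at one visit, 140 per arm.** Power = Φ(0.3/√(2v/140) − 1.96), with v the relative variance. For v = 1 this is Φ(2.51 − 1.96) = 71%.

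| r | follow-up only | change | adjusted |
|---|---|---|---|
| 0.5 | 71% | 71% | 83% |
| 0.6 | 71% | 80% | 88% |
| 0.7 | 71% | 90% | 94% |

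These figures are for the t-test. The rank-sum test also makes no use of baseline unless it is run on changes.

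**Step 3: false positives if each of six visits were tested at 0.05.** Independent visits: 1 − 0.95⁶ = 26.5%. Six equally correlated test statistics, by simulation: about 21% at correlation 0.5, 19% at 0.6, 16% at 0.7 and 14% at 0.8. This step applies only if visits are tested separately and any one significant result is claimed.

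**Step 4: possible loss of scores by week 24.** Week 24 is about 5.5 months. If the section 2.9 medians are taken as exponential from randomisation, the share with a DFS event by then is 1 − 2^(−5.5/19.3) ≈ 18% in controls and 1 − 2^(−5.5/31.3) ≈ 12% on test. Patients without course-6 questionnaire scores could thus be a visible fraction, and an unequal one.

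**The case against.** The strongest reply is that this is an open list in a condensed article. The sentence says "rank-sum test, among others, will be employed to analyze measurement data", so it does not confine the outcomes to two tests, and the full protocol or SAP may already name a suitable model. This stands against any statement that the trial will analyse these outcomes by t-test alone. It does not remove the point that the methods actually named are the less efficient ones and that nothing in the text points to a longitudinal model.

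A reader might infer four stronger things that the article does not support:

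- **That baseline is discarded.** The text does not say which quantity is tested. A t-test can be run on change from baseline, and against that comparator the saving at r = 0.7 is 15%, not 49%.
- **That every visit will be tested.** Table 1 is a schedule of collection, not of analysis. The 14-21% is conditional.
- **That all these outcomes have six post-baseline values and stop at recurrence.** CT is ticked at lead-in and only from the end of course 3, although the fat areas are read from CT and the fat-index row is ticked at every course. LMR, LNR and the prognostic nutritional index have no row of their own. Tumour markers and fat indices continue in follow-up, so the loss of values is best supported for the two questionnaires.
- **That a mixed model cures informative loss.** It relies on missing at random.

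It is also true that, under randomisation and with complete data, a two-sample test at one prespecified visit is valid; it is only less precise.

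**Conclusion.** The point holds as a concrete improvement on the method named, not as an error that invalidates an analysis. For repeatedly measured continuous secondary outcomes, the article names two-sample tests in an open list and no baseline-adjusted or longitudinal method.

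Under assumed correlations of 0.5 to 0.7 and equal variances, the avoidable variance is 25-49% against a follow-up-only t-test and 25-15% against a change-score t-test. The inflation of false positives rests on a visit-by-visit testing plan that the article does not state. The consequence is confined to secondary outcomes.

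**What to change.** In section 2.14 or the SAP, and before unblinding:

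- Make the main analysis of each continuous secondary outcome a mixed model for repeated measures with baseline value, arm, visit and arm-by-visit, over the visits at which that outcome is scheduled.
- Name one contrast per outcome in advance, such as the arm difference at the end of course 6.
- Log-transform skewed markers.
- Keep the t-test and rank-sum test as supportive analyses.
- Add a sensitivity analysis for scores lost after recurrence, because the model assumes missing at random.
- State which visits supply the CT fat areas and the LMR, LNR and nutritional index values.

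The cost is wording and somewhat more analysis work. SAS 9.4, already named in the article, fits the model with a standard procedure, and no new data are needed.
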